##### Implementation fidelity and quality monitoring

Implementation quality will be monitored by measuring and checking fidelity to implementation strategies. We conceptualize implementation fidelity similarly to intervention fidelity in that the primary measures of implementation fidelity are designed to index to what degree core functions of the implementation strategies are achieved. We also measure to what degree core elements (i.e., practices and processes) of each implementation strategy are conducted as planned, and whether any adaptations are fidelity consistent (done to maintain core functions) or inconsistent (drifting away in a manner unlikely to maintain core functions).

#### Rewards for questionnaire completion

The adolescents will accumulate monetary compensation as they submit questionnaires. Each submitted EMA/Daily diary yields 4 NOK (approx. 0.4$), and they will be compensated with 50 NOK (approx. 4.5$) for completing T1, T2, and T3. The accumulated compensation will be awarded at the end of the study as a universal gift card. The adolescents will have access to a graphic token system displaying how many submissions they have completed and the accumulated value of the gift card through the questionnaire links they receive by SMS. Additionally, the adolescents will be awarded a cinema gift card after completing T4. The Norwegian Regional Committees for Medical and Health Research Ethics evaluated this reward system and found it appropriate compensation for the adolescents’ time.

### Data analysis

#### Quantitative analyses

We will be analyzing the data from the adolescents descriptively and at the individual level using appropriate analyses for single-case experimental designs (e.g., autoregressive integrating moving average analyses; ARIMA) and at the group-level using appropriate intensive longitudinal analyses (e.g.,multilevel modeling, dynamic structural equation modelling; DSEM), accounting for gender and age. Analyses will be informed by the conceptual model to investigate associations between the elements the adolescents are given and change in specific emotion regulation strategies. We will use repeated measures ANOVA to compare group pre-, post-, and follow-up means on adolescents’ emotion regulation and mental health outcomes, and mixed models for testing multilevel associations between nurses’ intervention fidelity and adolescents’ outcomes. Data about implementation determinants will be analyzed descriptively. We will assess the extent of missingness, and explore the possible reasons for missing (e.g., missing not at random or missing at random). Missingness in experience sampling data will be handled by implementing full information maximum likelihood. Missingness in pre-, post-, and follow-up data will be handled using multiple imputation. The percentage of compliance of intensive longitudinal data will also be assessed.

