**Methods:**

The study employs a mixed-methods approach, integrating intensive longitudinal experience sampling (daily measures for 13 weeks), a micro trial, pre-, post-, and follow-up measures, audio recordings, and qualitative interviews to triangulate data from school nurses and adolescent participants. The research questions span the domains of intervention implementability, barriers and facilitators to implementation, proximal outcomes for adolescents’ emotion regulation, the mechanisms driving the intervention’s proximal effects, and response burden in experience sampling. The study aims to recruit a minimum of 25 health nurses and 46 adolescents.

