**Discussion:**

The study is novel in using mixed methods from multiple theoretical paradigms to examine ER as a dynamic process and transdiagnostic target outcome for promoting mental health and preventing disorders. Through daily diary and ecological momentary assessments, the study explores the intricacies of ER in real-life settings. Coupling the experience sampling with highly detailed fidelity measurement, we will observe adolescents’ day-to-day responses to intervention elements and how they affect emotion regulation. The integrated micro-trial also addresses concerns about response burden in experience sampling to optimize data collection strategies for future studies.

The findings from this study can increase our understanding of ER as a mental health process, and contribute to the development of scalable, efficient, and context-appropriate mental health interventions in school nursing.

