## Methods

### Setting

The study is conducted in school health services serving Norwegian lower (grades 8–10) and upper secondary schools (grades 11–13). The school health service work on directions and guidelines from the Norwegian Directorate of Health, and their main mandate is to promote health and well-being and prevent disease. All 8th graders have a mandatory consultation with school nurses to have a physical checkup and talk about health literacy and general coping. School nurses work on individual, group, and universal levels and offer a range of services, from individual consultations to classroom health literacy teaching and vaccination. Most school health services have 1–4 school nurses serving 1–5 schools, and the school nurses are typically located at the schools. Adolescents can visit the school nurses whenever they need to during school hours. They typically come to talk about peer and family issues, health-related questions and concerns, sex and contraceptives, and bullying. The last decade has seen a marked increase in adolescents visiting school nurses expressing trouble coping with emotions and stress [26]. However, school nurses have limited or no formal training in mental health prevention and intervention.

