### Data collection and outcomes

Table 3 depicts outcomes, instruments, data collection methods, informants, and time points for all measures used in the study. The time points correspond to two weeks prior to the start of the intervention (T1), once the adolescent completes the intervention (dynamic post measure, T2), 11 weeks after the intervention begins (T3), and again 11 weeks after T3 (T4) to serve as pre- post- and follow up assessments, respectively. The experience sampling measures will have a two-week baseline assessment between T1 and the intervention start.

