##### Adolescents’ proximal emotion regulation

(1) Daily experiences of affect and emotion regulation strategies will be measured using a daily diary, given every evening during the data collection period. (2) Momentary affect and emotion regulation strategies will be measured using momentary ecological assessment (EMA). Half of the sample will be randomized to daily diary only. The other half will be randomized to also report on momentary affect and emotion regulation strategies three times a day for four days every other week over two months (experience sampling period). Randomization is implemented digitally using sequential numbering in blocks of two participants (the first participant in the block is given a random value of 0 or 1, and the second is given the remaining value). There is no human assignment to conditions, the randomization result is automatically implemented by the data collection system. Supplementary file 2 depicts the data collection infrastructure and provides technical specifications of the experience sampling system.

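### Any day-level link between Kort elements and diary outcomes is confounded with the school-day/weekend cycle; gender and age cannot remove this, but a date-derived weekend term can

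*Protocol article*

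**What the plan says.** The Discussion part of the abstract says that experience sampling, coupled with detailed fidelity data, will let the study observe adolescents' "day-to-day responses to intervention elements and how they affect emotion regulation". The background section on emotion regulation as a dynamic process gives the reason: pre-post data alone cannot show when change happens or which element it follows. The Intervention fidelity section provides the link. A nurse's report after a consultation triggers element-specific items that the adolescent receives with that day's diary.

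Quantitative analyses names ARIMA for individuals and multilevel models or DSEM for the group, all as examples. With the conceptual model as guide, it will "investigate associations between the elements the adolescents are given and change in specific emotion regulation strategies". The adjustment named is "accounting for gender and age".

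On timing, Setting states that "the school nurses are typically located at the schools" and that "Adolescents can visit the school nurses whenever they need to during school hours". The diary is "given every evening during the data collection period". The abstract gives "daily measures for 13 weeks", and Data collection and outcomes places within this a "two-week baseline assessment between T1 and the intervention start", which leaves 11 weeks of sampling from the start of the intervention to T3. The article does not mention day of week, weekends or school holidays.

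**The concern.** Exposure (an element delivered in a consultation) can in practice occur only on school days, while the outcome is recorded on all seven days. A model that relates the diary to whether an element was delivered that day, or the day before, therefore also compares school days with weekends. The article itself says that the choice of regulation strategy depends on context and varies from day to day, and school versus no school is an obvious recurring change of context.

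Gender and age are constant, or nearly so, within an adolescent over 13 weeks. They can explain differences between adolescents, but they cannot act on a contrast between days of the same adolescent. In a single-person ARIMA model they are absorbed into the constant.

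What is at stake is the reading of element-level signals. If weekends are easier, an element can look inert or harmful on the day it is used. If weekends are harder, it can look helpful.

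**Working it through.** The article gives no figure for this point, so there is none to reproduce. The check asks how unbalanced the days are and what that does to a day-level contrast.

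**Inputs from the article.** Sampling lasts 13 weeks = 91 days. Baseline is 2 weeks = 14 days, 4 of them weekend days. The intervention period is 11 weeks = 77 days, 22 of them weekend days. From the power section: n = 40, intercept variance 0.7 and residual variance 0.3, which sum to 1, so outcome units are total SDs.

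**Assumptions not in the article.** Consultations fall on Monday to Friday only (inferred from Setting). Each adolescent has 5 or 11 consultations. The weekend shift w is 0.1 to 0.3 SD. The true element effect is zero.

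1. Weekend share of consultation days: 0%.
2. Weekend share p of the other days in the 77-day period: 22/(77 − 5) = 22/72 = 30.6%, or 22/(77 − 11) = 22/66 = 33.3%. Counting baseline days among the other days changes little: 26/86 = 30.2% and 26/80 = 32.5%.
3. Same-day contrast (consultation days minus other days): bias = w × (0 − p) = −w·p.
4. Next-day contrast: with consultations spread evenly over Monday to Friday, one in five is followed by a Saturday. For 5 consultations the difference in weekend share is 0.20 − 21/72 = −0.092. For 11 it is 0.20 − 19.8/66 = −0.100. At w = 0.3 the bias is −0.028 to −0.030.

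A within-person regression simulation (500 runs per cell, two-sided 5% level, independent residuals, the same weekend shift for everyone) agrees with these formulas. Each cell gives the values for 5 / 11 consultations:

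| Weekend shift w | Formula bias, same day | Simulated bias, same day | False positives, same day | Simulated bias, next day | False positives, next day |
|---|---|---|---|---|---|
| 0.1 | −0.031 / −0.033 | −0.030 / −0.034 | 11% / 22% | −0.010 / −0.010 | 3% / 8% |
| 0.2 | −0.061 / −0.067 | −0.064 / −0.067 | 37% / 65% | −0.021 / −0.019 | 7% / 11% |
| 0.3 | −0.092 / −0.100 | −0.089 / −0.100 | 55% / 94% | −0.029 / −0.031 | 11% / 17% |

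With w = 0 there is no bias. With a weekend term in the model, the same-day bias lies between −0.003 and 0.002 and false positives between about 2% and 7% for every shift tried.

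**Contrasts that stay balanced.** Baseline versus intervention period: 4/14 = 22/77 = 28.6% weekend days in each. One element versus another: both are delivered on school days, so the weekend share is 0% on both sides. The T1 to T4 questionnaires do not depend on consultation days.

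These figures are for the diary. EMA runs in four-day bursts, and the article does not say on which weekdays they fall, so the imbalance there cannot be computed.

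**The case against.** The strongest reply is that the contrast examined here is never written down. Quantitative analyses speaks of elements given and change in strategies; it does not say that consultation days will be compared with other days. The wording about responses from day to day comes from the abstract and states an ambition, not an estimand. The models are examples, any of them can carry a weekly term, and the text does not say that gender and age are the only covariates. A full covariate list is something a condensed article may leave to an analysis plan. Kort also trains skills, so its effects may build up over weeks and not show on one evening.

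Most of this stands. The point is therefore conditional on a day-level analysis, and it is not a charge that a stated rule is wrong. It does not dispose of the matter. The same-day link between consultation and diary is built into data collection, daily response is a stated purpose, and the one adjustment that is named cannot act on a within-person contrast.

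A reader might also infer that the analysis of mechanisms (research question 3.3) is compromised. The article assigns no particular analysis to that question, so this does not follow.

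**Conclusion.** The point holds in a limited form, as an improvement to the stated adjustment. If associations between elements and daily outcomes are estimated same-day or next-day, any weekly cycle is mixed with element delivery. The same-day bias is about 0.31 to 0.33 times the weekend shift, that is 0.03 to 0.10 SD for an assumed shift of 0.1 to 0.3 SD. For a next-day contrast it is roughly a third of that. It is zero if affect and regulation have no weekly cycle.

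This rests on consultations being confined to school days, which Setting makes very likely but does not state outright, and on a weekend shift that the article does not give. The false-positive rates depend on the same assumptions and on an analysis model that the article leaves open.

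Two stronger readings are not supported. A reader might infer that the overall effect of Kort is confounded by weekends. It is not, because baseline and intervention period are whole weeks with the same weekend share. A reader might also set the bias against the planning effect of d = 0.3. That effect belongs to the before-after contrast in the power section, which is unaffected, so the ratio would describe no planned analysis.

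**What to change.** In any multilevel, DSEM or ARIMA model that relates consultation elements to daily diary or EMA outcomes, add a school-day/weekend (or day-of-week) term. Alternatively, compare consultation days only with the same adolescent's other school days. One added sentence in Quantitative analyses is enough.

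The cost is one extra fixed effect, or one regressor in each individual model. The weekend indicator comes from the diary date, so no new data are collected. Treating school holidays as non-school days as well would need the school calendar. The whole-week phase comparison and the T1 to T4 analyses need no change.

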#### Qualitative analyses

The audio-recordings of consultations between school nurses and adolescents will be transcribed verbatim and coded for fidelity based on the “flexibility for function” conceptualization of fidelity. We will code quality in working towards core functions of intervention elements, and what components (i.e., activities and exercises) were used with adolescents in the consultation. We will also code which problems and concerns the adolescent brings to the consultations, how working goals are formulated, as well as communication structure and quality, and common relationship factors such as trust, alliance, and empathy. In addition, we also will code adolescents’ expressions of emotional concerns using a validated and widely used coding tool; Verona Definition of Emotional Sequences (VR-CoDES [65]).

The interviews with adolescents will be transcribed verbatim and coded for their experiences with the intervention and experience sampling. We will analyze the transcribed interviews using inductive, reflexive thematic analysis [66]. The analysis will use the six-phase process for data engagement, coding and theme development by Clarke & Braun [66]: (1) data familiarisation; (2) systematic data coding; (3) generating initial themes from coded and collated data; (4) developing and reviewing themes; (5) refining, defining and naming themes; (6) writing the report.

The focus group interviews in the implementation planning were transcribed verbatim and analyzed thematically with a combination of inductive and deductive coding based on the COM-B theory of behavior and motivation [53] the Consolidated Framework for Implementation Research 2.0 [52], and implementability theory [33].

#### Mixed-methods analyses

The mixed methods design employed in the study is used with dialectical pluralism as a philosophical foundation [67]. Thus, quantitative and qualitative results will be merged in tables, and results from each data source will be compared for convergence or divergence, interpreted from different paradigmatic perspectives, and integrated or synthesized using dialectics [67]. Qualitative results will also be used to complement the quantitative results to provide a more in-depth understanding of findings, mechanisms of change, and lived experiences.

#### Power calculation for daily diaries

Power calculations were done using simulations in R with a sample of *n* = 40. With 10 measurement points before and 10 after the intervention, the power to detect a true effect of the intervention of *d* = 0.3 is 70%. Power increases to 80% with 20 measurement points before and after the intervention. With 10 measurement points before and after the intervention, power is 100% when the effect of the intervention is *d* = 0.5. These numbers apply when the variance of the effect of the intervention (slope) is 0.3, the variance of the initial level of the outcome variable (intercept) is 0.7, and the residual variance of the outcome variables is 0.3. We expect up to 15% dropout and will thus recruit a minimum of 46 adolescents to reach the minimum of 40 complete cases.

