### Procedures

#### Recruitment

School school nurses will be convenience sampled through social media outreach and through a network of Norwegian municipalities organized by the study partner Fremsam, the Norwegian faction of the World Health Organizations’ Healthy Cities Network [44]. School nurses and leaders of school health services expressing interest will be invited to online information meetings. The leader of the school health service must sign a collaboration agreement before their school nurses can provide informed consent for participation.

The school nurses will be responsible for recruiting 1–5 eligible adolescents each and obtaining signed consent forms from the adolescents and their primary caregivers. Eligible adolescents will be identified through the mandatory 8th -grade consultation or by self-initiating support from a school nurse. Recruitment takes place in the following steps for adolescents under the age of 16:

The nurse determines whether the adolescent is eligible (mild to moderate mental health challenges).If eligible, the school nurse provides the adolescent with oral and written information about the Kort study and invites them to participate.If the adolescent consents orally, information and consent form will be distributed to the primary caregiver(s) by the school nurse via an SMS containing a link to the study’s website with additional information. The adolescents also receive an information pamphlet to take home with information and a QR code to the study’s website.On the website, the caregiver can give informed consent for both caregivers or only for themselves and provide contact information for the other caregiver.If applicable, an SMS is then sent to the other caregiver with information and a link to the website and consent form.

If the adolescent is aged 16 or older, steps a and b will be the same. In step c, if the adolescent consents orally, information and a consent form will be distributed to the adolescent by the school nurse via an SMS containing a link to the study’s website and a consent form with information tailored to their age group. The adolescent receives a pamphlet to take home, with study information and a QR code to the study’s website. Informing parents about the study is voluntary. Adolescents may be recruited consecutively throughout the study period and until two months prior to the end of the study.

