#### Personalization and flexibility

The intervention structure is modeled after the principles of *Flexibility for Function* [33]. This is an operationalization of evidence-based practice through the ethically conscious integration and interdependence of evidence-based intervention elements, functions, and components, professional skills and autonomy, and optimizing personalization and adaptations. The training and handbook include specific sequences and combinations of elements that are considered helpful for different types of challenges adolescents typically face. However, school nurses will be trained in and encouraged to personalize the structure to the adolescents’ needs/goals, circumstances, and preferences, as well as making adjustments based on progress. Also, school nurses will be trained to defer to the components of each element as evidence-informed go-to strategies for working towards achieving the elements’ core functions. However, they are also encouraged and trained in making what they consider optimizing adaptations to these components (i.e., adaptations that increase the likelihood of achieving core functions) based on both planned and in-the-moment considerations of individual and contextual circumstances.

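### The repeated measures ANOVA planned for the effectiveness outcomes has no nurse term, although each nurse treats 1–5 adolescents; if change correlates within nurse, its standard errors are too small

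*Protocol article*

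**What the plan says.** Under Recruitment, each nurse is "responsible for recruiting 1–5 eligible adolescents each". Participants and criteria sets targets of 25 nurses and at least 46 adolescents. Kort is delivered in individual consultations with the nurse, and under Personalization and flexibility "school nurses will be trained in and encouraged to personalize the structure".

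The section Effectiveness of the intervention, placed under the primary outcomes, lists DERS-SF, BFS and SWEMWBS at T1 to T4. For these questionnaire outcomes, Quantitative analyses says: "We will use repeated measures ANOVA to compare group pre-, post-, and follow-up means". No nurse term is mentioned. The same paragraph does plan mixed models linking nurses' fidelity to adolescents' outcomes. The group-level diary data are assigned to multilevel models or DSEM, given as examples, with gender and age the only named adjustments and the levels not stated.

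The section Power calculation for daily diaries opens with "Power calculations were done using simulations in R with a sample of" 40. It gives 70% for d = 0.3 with 10 points before and 10 after, then "Power increases to 80% with 20 measurement points before and after the intervention", and 100% for d = 0.5. The conditions are: "These numbers apply when the variance of the effect of the intervention (slope) is 0.3", intercept variance 0.7 and residual variance 0.3. No nurse-level variance is listed.

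**The concern.** The effectiveness comparison has one group, and its estimand is the mean within-adolescent change. Stable differences between nurses in the level of their adolescents drop out of that change. Differences between nurses in how much their adolescents change do not, and they add to the variance of the mean change.

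The protocol itself gives reason to expect such differences. It links fidelity, competence and alliance to emotion regulation processes, has supervisors contact nurses with persistently low function scores, and plans a model relating nurse fidelity to outcome. It thus recognises the nesting for the fidelity question but names a method without it for the effectiveness question. At stake are confidence intervals that are too narrow and a type I error above the nominal level on outcomes listed as primary.

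**Working it through.** **Inputs from the protocol.** 40 complete cases; 25 nurses; 1–5 adolescents per nurse. Averages: 46/25 = 1.84 recruited and 40/25 = 1.6 complete per nurse.

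**Assumed.** Within-nurse ICC of change 0.05–0.20 (none is given); two-sided 5% (no alpha is stated). The two splits of 40 adolescents over 25 nurses are constructed for illustration.

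**Design effect for the mean change.** DE = 1 + ICC × (Σm²/Σm − 1), where m is the number of adolescents per nurse.

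- Even: 15 nurses with 2 and 10 with 1. Σm² = 60 + 10 = 70, and 70/40 = 1.75, so DE = 1 + 0.75 × ICC.
- Uneven: 2 nurses with 5, 2 with 3, 3 with 2 and 18 with 1. Σm² = 50 + 18 + 12 + 18 = 98, and 98/40 = 2.45, so DE = 1 + 1.45 × ICC.

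**Type I error of an analysis that ignores nurse.** For a single before-after contrast with 39 df, true alpha = 2 × P(t₃₉ > 2.023/√DE). The correct SE is √DE times the unadjusted SE.

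| Split | ICC | DE | √DE | True alpha |
|---|---|---|---|---|
| Even | 0.05 | 1.04 | 1.02 | 5.4% |
| Even | 0.10 | 1.08 | 1.04 | 5.8% |
| Even | 0.20 | 1.15 | 1.07 | 6.7% |
| Uneven | 0.05 | 1.07 | 1.04 | 5.8% |
| Uneven | 0.10 | 1.15 | 1.07 | 6.6% |
| Uneven | 0.20 | 1.29 | 1.14 | 8.3% |

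If only 15 nurses recruited (3 with 5, 2 with 4, 3 with 3, 1 with 2, 6 with 1; 144/40 = 3.6), DE would be 1.13–1.52 and true alpha 6.4–10.9%. A 20,000-run simulation of an unadjusted paired test agrees in size: 5.5–6.7% with an even split over 25 nurses, and 5.9–8.7% with the most uneven split possible (size-weighted mean 2.8).

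**The diary power figures.** With independent adolescents, the variance of the mean effect is (slope variance + 2 × residual variance/points per phase)/n. The intercept cancels.

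- d = 0.3, 10+10 points: (0.3 + 0.06)/40 = 0.009, SE 0.0949, noncentrality 0.3/0.0949 = 3.16. Power is 86.9% by noncentral t (88.5% by normal approximation), against 70% stated.
- d = 0.3, 20+20 points: (0.3 + 0.03)/40, SE 0.0908. Power is 89.6%, against 80% stated.
- d = 0.5, 10+10 points: power is 99.9%, in line with the stated 100%.

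Other scalings of d and other alphas did not give 70% and 80% together. Applying the design effect to the slope variance, by normal approximation for d = 0.3 with 10+10 points, gives 84–88% at 1.6–1.84 adolescents per nurse for ICC up to 0.20. With five per nurse it gives 83%, 78% and 69% at ICC 0.05, 0.10 and 0.20.

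**The case against.** **The effect is small at the planned cluster size.** Five per nurse is a maximum. At 1.6–1.84 per nurse and ICC 0.05 the standard error is only about 2% too small. This stands. Larger figures need a higher ICC or concentrated recruitment. Neither is given in the protocol, although it does foresee halts in recruitment and nurses withdrawing.

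**Personalisation may not produce a high ICC.** Elements are tailored to the adolescent, so delivery also varies within a nurse. This stands as a reason not to presume a high value, but it does not make the ICC zero.

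**The diary models may already carry a nurse level.** The methods are named as examples and the levels are neither stated nor excluded, and an article may leave them to a fuller plan. This stands for the diary models. It does not cover the ANOVA, which is a stated choice.

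**The power figures do not belong to the ANOVA.** The power section concerns the daily diaries only. This stands. A reader might infer from the missing nurse variance that the stated 70% and 80% are too high. The documents do not support that: the printed variances give about 87% for the 70% case, and with clustering added, power falls below 70% only in the extreme case of five per nurse and ICC 0.20. Figures below 70% otherwise arise only by taking the 70%, which could not be reproduced, as the starting point and discounting it.

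**A nurse random effect may be hard to estimate.** In the two splits above, 10 or 18 of the 25 nurses have a single adolescent. This stands, and the fix needs a fallback.

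**Conclusion.** The point holds for the questionnaire outcomes. The named ANOVA ignores nurse, and its standard errors are too small if change correlates within nurse. Assuming an ICC of change of 0.05–0.20, true alpha at a nominal 5% is about 5.4–6.7% with even recruitment and 5.8–8.3% with uneven recruitment over 25 nurses. The lower end is the likelier one if recruitment stays near the planned average and the ICC is modest. The alpha figures are for a single before-after contrast; the overall F test across time points was not computed.

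For the diaries, the conclusion is limited to a condition: the simulation lists no nurse variance, so its power figures apply only if change is uncorrelated within nurse. Whether the stated power is too high in absolute terms is not shown.

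**What to change.** 1. In Quantitative analyses, replace the repeated measures ANOVA with a linear mixed model: time as a fixed factor, repeated measures within adolescent, and a nurse random effect on change. State in advance that if the nurse variance cannot be estimated, nurse-clustered standard errors with a small-sample correction will be used.
2. State that the group-level diary models use the same nurse level or clustered errors.
3. In the power section, add that the figures assume no within-nurse correlation of change, or rerun the simulation with a nurse-level slope variance and 1–5 adolescents per nurse and report power over a stated ICC range. Give the alpha and the scale of d at the same time, so that the figures can be reproduced.

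The cost is a change of analysis wording and, if chosen, one rerun of an existing simulation. The nurse's fidelity report after each consultation already triggers the matching adolescent questionnaire, so the linkage exists. The downside is slightly wider intervals. No extra recruitment is needed.

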### Participants and criteria

We aim to recruit 25 school nurses from school health services serving either lower or upper secondary schools, or both. The school health services will be located in both rural and urban areas in the southeastern region of Norway. We aim to recruit a minimum of 46 adolescents in lower secondary school (age 12–16) and upper (age 16–18). Adolescents aged 12–15 will need informed consent from primary caregivers to participate. Adolescents aged 16 or older will provide informed consent on their own behalf. Consent forms are available in Supplementary file 3.

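### The recruitment minimum of 46 matches 40 × 1.15; at a 15% dropout rate it yields an expected 39.1 complete cases, and 40 remain only if at most 6 adolescents (13.0%) drop out

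*Protocol article*

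**What the plan says.** The section on the power calculation for daily diaries bases its simulations on 40 adolescents. At that size it reports the following power:

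- 70% for d = 0.3 with 10 measurement points before and 10 after the intervention
- 80% for d = 0.3 with 20 points before and after
- 100% for d = 0.5 with 10 points before and after

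It then moves from the analysed number to the recruited number in one sentence: "We expect up to 15% dropout and will thus recruit a minimum of 46 adolescents to reach the minimum of 40 complete cases". The word *thus* presents 46 as following from 40 and 15%. No inflation formula is given.

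The same minimum appears in two other places. The abstract states "The study aims to recruit a minimum of 25 health nurses and 46 adolescents", and the section on participants and criteria states "We aim to recruit a minimum of 46 adolescents in lower secondary school". Neither of these mentions dropout or complete cases.

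The section on quantitative analyses says that missing experience-sampling data will be handled by full information maximum likelihood.

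**The concern.** Dropout is a proportion of those recruited. To end with 40 after losing 15%, one divides 40 by 0.85. Multiplying 40 by 1.15 applies the percentage to the wrong base and gives a number that is slightly too small. The stated 46 coincides exactly with that product.

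What is at stake is the consistency of the sample-size rationale. Every power figure in the section is given at 40, and 46 is offered as the minimum that secures 40 at the dropout the authors allow for. If 46 secures 40 only at a lower dropout, the sentence claims a little more tolerance than the plan has. There is also little slack to absorb this, since power for d = 0.3 with 10 points before and after is already only 70%.

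**Working it through.** **Inputs**, all from the power section: 40 complete cases required, dropout up to 15%, at least 46 recruited, and power of 70% and 80% at 40 for d = 0.3.

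**1. Reproducing the stated figure.** 40 × (1 + 0.15) = 46.0, an exact match.

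**2. Inflating for a 15% loss among recruits.** 40 / (1 − 0.15) = 40 / 0.85 = 47.06. Rounded up, this is 48, two more than stated. In expectation, 47 recruits leave 47 × 0.85 = 39.95 and 48 leave 48 × 0.85 = 40.8.

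**3. What 46 delivers at a 15% rate.** 46 × 0.85 = 39.1 expected complete cases.

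**4. What dropout 46 can bear.** 46 − 40 = 6 losses, and 6/46 = 13.0%. One more loss gives 7/46 = 15.2% and leaves 39.

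**5. Chance of reaching 40.** Assume that each recruit drops out independently with probability 0.15 (an assumption; the article gives no model for dropout). The binomial probability of at least 40 completers is then:

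| Recruited | Expected completers | P(at least 40) |
|---|---|---|
| 46 | 39.1 | 0.45 |
| 47 | 39.95 | 0.59 |
| 48 | 40.8 | 0.71 |

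**6. Effect on power of 39 instead of 40.** Assume a two-sided 5% level (not stated in the article) and a normal approximation in which the noncentrality scales with the square root of the sample size. The factor is √(39/40) = 0.987.

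- 70%: noncentrality 0.524 + 1.960 = 2.484; 2.484 × 0.987 = 2.453; 2.453 − 1.960 = 0.493; power 68.9%.
- 80%: noncentrality 0.842 + 1.960 = 2.802; 2.802 × 0.987 = 2.766; 2.766 − 1.960 = 0.806; power 79.0%.

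The loss is about 1 percentage point in each case. The 100% figure for d = 0.5 was not recalculated; one case fewer would hardly move it.

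**The case against.** The strongest defence reads the sentence in whole persons. It gives dropout as a ceiling ("We expect up to 15% dropout") and recruitment as a floor. With 46 recruited, 6 losses are 13.0% and 7 are 15.2%, already above the ceiling. So at most 6 can be lost, exactly 40 remain, and 46 is the smallest number that works, since 45 recruits with 6 losses (13.3%) leave 39. Read literally, this is correct. A reader might infer from the arithmetic that the sample-size claim is simply false, or that the plan ends with 39 cases. The article does not support either statement that flatly, because 39 requires a seventh dropout or a rounded expectation at the ceiling rate. What the defence does not remove is that a planning rate is not normally a guaranteed cap on a head count. At a true rate of 15%, 46 recruits are more likely than not to miss 40.

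Second, the multiply-up origin is an inference. No formula is printed, and the whole-person count also arrives at 46. The exact match with 40 × 1.15 is suggestive and no more.

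Third, full information maximum likelihood lets an adolescent who leaves early contribute the diary days already given, so a dropout does not remove a whole case from the diary analysis. This stands and softens the effect on power. It does not repair the sentence, which sets its own criterion in complete cases.

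Fourth, 46 is a minimum. With 25 nurses recruiting 1–5 adolescents each, the plan has room for 25 × 5 = 125. That is so, but the sentence says that the minimum itself is enough.

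**Conclusion.** The point holds as a minor error in a figure that the article states and relies on. At a 15% dropout rate, 46 recruits fall just short of 40 complete cases in expectation (39.1), and the tolerance that 46 really provides is 6 dropouts, or 13.0%. The arithmetic uses only the article's own numbers.

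The consequence is small: about 1 percentage point of power, under an assumed two-sided 5% level and a square-root scaling of the noncentrality, and probably less given the planned handling of missing diary data. The 45% chance of reaching 40 rests on the added assumption of independent dropout at exactly 15%.

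A reader might go further and conclude that the study is underpowered or that 48 must be recruited. Neither follows. A shortfall of one case does not change any planned analysis, and 48 is needed only if 40 complete cases and a 15% dropout rate are both to stand as an expectation.

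**What to change.** Keep 46 and restate the one sentence in the power section in either of two ways:

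- *46 recruited allows up to 6 dropouts (13%) for 40 complete cases.*
- *46 recruited; about 39 complete cases expected at 15% dropout*, with the power figures restated at n = 39 by rerunning the existing simulation.

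The abstract and the participants section need no change, because they give only the recruitment minimum, which stays at 46. The first option costs a change of wording and makes the stated dropout tolerance slightly less favourable. The second adds a rerun of the simulation. Neither calls for further recruitment or a change to the analysis.
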